We hypothesize that a) volume of participation and b) duration of participation will correlate positively with the primary outcomes listed above.

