## Methods/design

### Study design

The MLSE LaunchPad trial employs a single-arm, non-randomized within subject quasi-experimental design following a cohort of 350 participants aged 6–29 years old over up to 2-years of self-selected participation in programming at MLSE LaunchPad, a Sport for Development facility in downtown Toronto, ON, Canada. Data collection methods utilize repeated measures of age-specific outcomes according to hypotheses outlined in Table 1 and further described in Table 3 using self-reports and pedometer data at baseline, 6 months, 12 months, and 24 months from baseline. Qualitative assessments will take place annually throughout the data collection period using focus groups with a subset of participants. This protocol was developed in the fall of 2016 and initiated in February 2017. These data will collectively be used to evaluate the effects of intentional sport programming in a community hub on PYD and SFD outcomes in urban youth facing barriers. Moderating variables including age, gender, race, household income, postal code, program type, volume of participation and duration of participation will be explored to understand possible explanatory individual and programmatic elements of significance.

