Programs for the 6–12 and 13–18 year-old cohorts will be delivered in 8-week cycles with 5 cycles each year. As research participants may participate in multiple recreational programs concurrently, volume (total program hours) and duration (number of program weeks) of participation will be used as mediating variables in analyses to examine the dose-response on objectives outlined in Table 1. All programs will include life skills development using coaching strategies discussed by Camiré et al. (2011) [19], focused on 7 life skills identified in the MLSE LaunchPad Theory of Change: grit, resilience, self-esteem, self-regulation, critical thinking, social competence, and leadership.

Participants aged 19–29 years will be offered plus sport programming developed in collaboration with local community organizations offering occupational skills training and other employment services. These agencies will demonstrate strong histories of positive youth impact and will work with MLSE LaunchPad’s sport programmers to deliver integrated employment training and sport/physical activity programming. The addition of sport and physical activity is expected to offer a different context for reiteration of in-class themes (i.e. leadership and other key life skills) and to encourage increased long-term physical activity participation. The priority of this age group will be the Ready for Work pillar. Secondary emphasis will be on the Healthy Body and Healthy Mind pillars. Due to the training nature of these programs, the format will differ from the programs offered for youth aged 6–18, and programs will generally be delivered for 4 or more hours per day, 5 days per week for 8–10 weeks, with sport programming delivered in 1-h sessions 2 days/week.

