#### Data analysis

Preliminary analyses will be conducted after 6, 12, and 24 months of recruitment. All statistical analyses will be completed using either SPSS versions 24/25 (IBM) or *R*. Missingness in data will be evaluated for amount of missing data and patterns in missingness. Based on the results of this evaluation, a single mean value imputation method will be applied as needed.

*Ages 6–12:* Repeated measures ANOVAs will be used to examine the main effect of time on physical literacy scores, self-reported physical activity and rates of continued participation in physical activity, controlling for demographic variables such as age and gender. Moderation analyses will be used to explore the effect of program dosage in terms of the number of programs attended over the course of participation in this study on the relationship between time and change in physical literacy. A similar moderation effect will be explored in the relationship between time and the change in self-reported physical activity levels. Pearson’s product-moment correlation coefficients will also be used to explore the relationship between physical literacy and physical activity levels. A standard multiple regression controlling for age, gender, household income and housing status will be used to identify predictive variables for each of the three primary outcomes. Potential predictors for the change in physical literacy include program dosage, type of program involvement (Sport Plus or Plus Sport), physical literacy score at baseline and physical activity level. Potential predictors for the change in physical activity level and rate of continued participation in sport or physical activity include program dosage, type of program involvement, physical activity level at baseline and physical literacy score.

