*Ages 13–18:* Repeated measures ANOVAs will be used to examine the main effect of time on positive health behaviours and each of the six life skills, controlling for demographic variables such as age, gender, household income and race. Moderation analyses will be used to explore the impact of program dosage on the relationship between time and each of the six life skills. Pearson’s product-moment correlation coefficients will also be used to explore the relationship between each of the life skills, positive health behaviors and academic outcomes. Logistic regression will be used to identify predictors of high school graduation for the subset of this age group that would be expected to graduate during the study with possible predictors including scores for each life skill at 2-year follow-up, program dosage and program type, while controlling for gender, household income, housing status and baseline life skills score. The same variables will also be used in a standard multiple regression to identify predictors of continued participation in sport and physical activity in this age group.

*Ages 19–29:* Repeated measures ANOVAs will be used to examine the main effect of time on rate of employment, apprenticeship, or continued training, personal income, and rate of continued participation in physical activity, controlling for demographic variables such as age, education level, household income at baseline and housing status at baseline. Logistic regression will be used to identify predictors of employment status at 2-year follow-up, which may include program type and program dosage (number of programming hours), while controlling for similar demographic variables as identified above for the Repeated Measures ANOVA.

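### For ages 6–12, dose is analysed as a count of programs, which contradicts the hours and weeks set for the same cohort and measures neither quantity in the secondary hypothesis

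*Protocol article*

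**What the plan says.** The secondary hypothesis (Table 1) is that "volume of participation and b) duration of participation will correlate positively with the primary outcomes listed above".

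Core programming, in a paragraph covering ages 6–12 and 13–18, gives the reason for its dose measures, "As research participants may participate in multiple recreational programs concurrently", and then the measures: "volume (total program hours) and duration (number of program weeks) of participation will be used as mediating variables in analyses".

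The Data analysis section departs from this:

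- Ages 6–12: the moderation analysis of physical literacy uses "program dosage in terms of the number of programs attended over the course of participation in this study". A similar moderation is planned for physical activity, and the regressions for this cohort reuse the term program dosage.
- Ages 13–18: "Moderation analyses will be used to explore the impact of program dosage on the relationship between time and each of the six life skills". No unit is given.
- Ages 19–29: dose is a candidate predictor in a logistic regression and is counted in hours, "program dosage (number of programming hours".

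On the role of dose, Study design says "Moderating variables including age, gender, race, household income, postal code, program type, volume of participation and duration of participation will be explored". The Background and the Data analysis paragraphs for ages 6–12 and 13–18 also describe moderation. Core programming says mediating.

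**The concern.** Two sections give the same cohort different dose variables. The one in the analysis paragraph is neither of the quantities in the hypothesis. Core programming turns to hours and weeks because a child may attend several programs at once. A tally of programs does not meet that need, since programs differ greatly in length.

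The tally has two further faults. It accumulates over the whole of a child's participation, while the time available to accumulate depends on enrolment date. It also includes programs attended after the interim assessments whose change it is supposed to moderate.

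The role matters too. A moderator changes the size of the time effect, and a mediator lies on the path to the outcome. These need different models, and only moderation and regression are described.

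The study has one arm and follows growing children, so change over time alone says little about the program. The dose analysis is one of the few quantitative comparisons that bear on the difference, and its exposure variable should match the hypothesis.

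**Working it through.** **1. The plan's own figure.** The protocol gives no figure for the dose-response analysis. The only one for this cohort that can be recomputed is the 94.9% power for physical literacy. With d = (1277 − 1201)/258.8 = 0.294, n = 150 and an assumed two-sided 5% level, the one-sample normal approximation gives Φ(0.294 × √150 − 1.960) = Φ(1.637) = 0.949. It reproduces, but it concerns a mean difference and does not bear on this point.

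**2. Dose variable by section.**

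| Place | Cohort | Dose | Role |
|---|---|---|---|
| Table 1, secondary hypothesis | all | volume, duration | correlate |
| Study design | all | volume, duration | moderator |
| Core programming | 6–12, 13–18 | hours, weeks | mediator |
| Data analysis | 6–12 | count of programs | moderator, predictor |
| Data analysis | 13–18 | no unit | moderator, predictor |
| Data analysis | 19–29 | hours | predictor |

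The count at ages 6–12 is the outlier. Weeks are not named in the Data analysis section for any cohort.

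**3. Hours in one program, ages 6–12 (Table 2).**

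- Learn to Play: 8 × 1 h = 8 h.
- Sport + Nutrition: 9 × 2 h = 18 h.
- PA Day: one full day, 6–8 h (assumed day length).
- Day Camp: two weeks of full days, 10 × 6–8 h = 60–80 h (assumed days and day length).

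One camp is therefore 60/8 = 7.5 to 80/8 = 10 times one Learn to Play course. Table 2 labels all four as Sport Plus. The program-type term in the regression has two levels, Sport Plus or Plus Sport, so it cannot adjust for this mix.

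**4. Available follow-up.** Recruitment runs from February 2017 to September 2019, data collection ends on March 31, 2020, and follow-up is at most 24 months. Core programming gives 5 cycles a year.

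| Enrolled | Maximum follow-up | Cycles (months/12 × 5) |
|---|---|---|
| up to March 31, 2018 | 24 months | 10 |
| March 31, 2019 | 12 months | 5 |
| September 2019 | 6–7 months | 2.5–2.9 |

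Between the extremes, the cycles on offer differ by 10/2.9 = 3.4 to 10/2.5 = 4 times at the same intensity of attendance.

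**5. Timing.** Take a child with 24 months of follow-up and steady attendance (assumed). Of 10 cycles, 2.5 precede the 6-month assessment and 7.5 follow it. For the 12-month assessment the split is 5 and 5. A whole-study count thus places 75% and 50% of the dose after the change being analysed. This holds even for children with every visit.

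**6. How much distortion?** The protocol has no attendance data, so this was simulated with assumed inputs: uniform enrolment over the window; 1 to 10 programs a year on average; a coefficient of variation of attendance between children of 0 to 1; two program mixes, varying between children; a 7 h full day; Open Gym left out.

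- Follow-up length explained 5–61% of the variance in the count, and 5–23% once the coefficient of variation was 0.5 or more.
- The count explained 29–71% of the variance in hours. Among children with a full 24 months available, it explained 12–70%.

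The count carries information about hours but is a noisy and partly time-driven stand-in. The size of the problem depends on data not in the document.

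**The case against.** The strongest reply is that the protocol already commits to the right variables. Core programming names hours and weeks for this cohort, Study design lists volume and duration for exploration, and the hypothesis matches both. On that view the count is a loose phrase in one sentence about secondary, exploratory analyses. It is fair that the hypothesis has matching variables elsewhere. But the analysis paragraph for ages 6–12 contradicts them, and an analyst following it would use the count.

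Several stronger readings are tempting and are not supported:

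- *The dose analysis mostly measures program mix and enrolment date.* The documents hold no participation data, and in the simulation follow-up length explained a minority of the count once children differed in attendance.
- *Dose has three rival definitions.* Hours and weeks are two declared dimensions matching the two parts of the hypothesis. Only the count clashes with them.
- *Children are misclassified up to 10-fold.* That is the spread between single programs. A child would reach it only by attending camps alone, compared with one attending Learn to Play alone.
- *Dose-response is the only internal evidence.* Program type is also a predictor and moderator, and focus groups address impact.

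If the repeated measures ANOVA keeps only children with all four visits, follow-up is about constant and the enrolment-date problem largely vanishes. With the planned mean imputation of missing values it could remain. The program-mix and timing problems stand either way. How drop-in Open Gym would be counted is not stated, but an article may leave that to the full protocol.

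On mediation, no mediation model is specified anywhere, and the similar wording under Incentivization is a rationale for rewards. That part is a matter of one word.

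**Conclusion.** The point holds as a contradiction in the text with a practical consequence. At ages 6–12 the count of programs conflicts with the hours and weeks set in Core programming and measures neither volume nor duration.

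The count is confounded by program mix, with 8 h, 18 h or about 60–80 h in one program, the last resting on an assumed 10 days of 6–8 h. It is also confounded by available follow-up of 6–7 to 24 months, unless only children with all visits are analysed. It includes participation after the 6- and 12-month assessments. The mediator label in Core programming does not match the moderation analyses described elsewhere.

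The degree of distortion in the eventual result is not established. The affected analyses are secondary and exploratory.

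**What to change.** - In the ages 6–12 analysis, replace the count with attended program hours (volume) and program weeks (duration), as defined in Core programming. Use the same definitions in all three cohorts, including ages 13–18, where no unit is given.
- Count dose only up to the assessment being analysed. A standard repeated measures ANOVA takes one fixed covariate value per child, so the simplest route is to analyse the change from baseline to each assessment against the dose accrued by then.
- Where follow-up still differs between children, include follow-up time in the model or add a sensitivity analysis of dose per unit of follow-up. The latter is intensity and should not replace total hours as the measure of volume.
- In Core programming, change mediating to moderating.
- Report the result as an association, because participation is self-selected.

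The cost is a few wording changes and slightly more analysis. No new data are needed for volume, since Incentivization says that program hours and attendance are already collected centrally. Weeks should be derivable from the attendance records.

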A large, long-term longitudinal study investigating PYD outcomes in a SFD facility for urban youth facing barriers that is based on a clear theory of change illustrating program components is therefore needed. This research is important for both theoretical and practical reasons, and addresses several future research directives published in the field including calls for mixed-methods, longitudinal, and evaluative studies that validate the development of life skills through sport and evaluate the impact of program type of PYD outcomes [26, 30–32]. The current study proposes that participation in theory-based SFD programming at a dedicated facility will lead to increased PYD outcomes in urban youth facing barriers to positive development with age-specific objectives outlined in Table 1 and further articulated in Fig. 1, the Maple Leaf Sports and Entertainment (MLSE) LaunchPad Theory of Change. Repeated measures ANOVAs will be used to explore the effect of long-term participation in MLSE LaunchPad programming on age-specific outcomes. Moderation analyses will be used to identify the impact of program dosage on the relationship between time and primary outcomes. Finally, regression analyses will be used to identify the predictors of primary outcomes to better inform programming.

**Table 1 Tab1:** Study Hypotheses

Primary Hypotheses	
We hypothesize that participation in MLSE LaunchPad programming and wrap around services will result in:	
a) For youth aged 6–12:	• Increased physical literacy • Increased physical activity [28] • Increased rates of continued participation in sport or physical activity [33]
b) For youth aged 12–18:	• Increased positive health behaviors relating to physical activity, sleep, nutrition, smoking, substance use and sexual activity [29, 34] • Increased life skills including critical thinking, resilience, self-esteem, self-regulation, social competence and grit [26] • Increase academic outcomes including school attendance, academic performance and high school graduation rates [26, 34] • Increased rates of continued participation in sport or physical activity [34]
c) For youth aged 19–29:	• Increased rates of placement in employment, apprenticeship, or continued training [26, 29] • Increased personal income • Increased rates of continued participation in sport or physical activity [34, 35]
Secondary Hypotheses	

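### Ages 6–12: the baseline score is listed as a candidate predictor of its own change, so its coefficient will lean negative through regression to the mean and cannot be read as differential benefit

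*Protocol article*

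**What the plan says.** The protocol article, Data analysis, ages 6–12, separates two kinds of variable. The adjustment set is given first: "A standard multiple regression controlling for age, gender, household income and housing status". That regression "will be used to identify predictive variables for each of the three primary outcomes". The candidates follow: "Potential predictors for the change in physical literacy include program dosage", then programme type, then "physical literacy score at baseline and physical activity level". For change in physical activity and for continued participation the candidates are "program dosage, type of program involvement, physical activity level at baseline and physical literacy score".

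Two other places bear on how the baseline term would be used. The Background says that "regression analyses will be used to identify the predictors of primary outcomes to better inform programming". For ages 13–18, the Data analysis section gives the baseline score an adjustment role only: "while controlling for gender, household income, housing status and baseline life skills score". The outcomes there are high school graduation and continued sport participation, not change in life skills, so that sentence is a precedent for the role of a baseline term and not for the same model.

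The article mentions neither regression to the mean nor the arithmetic link between baseline and change.

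**The concern.** A baseline score that is high partly by chance tends to be followed by a lower one, and a low score by a higher one. Because change subtracts baseline, any error or passing variation in baseline enters change with the opposite sign. A regression of change on baseline thus has a negative slope even when the programme does the same for every child. A single-arm study has no control group in which to see how much of that slope would arise without the programme.

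As an adjustment term this does no harm. The article, however, puts baseline on the list of variables to be identified as predictive, and the identified predictors are meant to guide programming. A significant negative coefficient invites the message that children who start low gain most, and these data could produce that message with no true differential gain.

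**Working it through.** **The plan's own figure.** The Sample size section gives, for ages 6–12, means of 1201 and 1277, SD 258.8, n = 150 and power 94.9%. With a one-sample normal approximation and two-sided alpha 0.05 (assumed, as none is stated): (1277 − 1201)/258.8 = 0.294; 0.2937 × √150 = 3.597; Φ(3.597 − 1.960) = 0.949. The figure reproduces. This point does not dispute it; the check only confirms that n and the SD have been read correctly.

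**Size of the artefact.** Assume equal variances at baseline and follow-up, the same true gain for every child, and baseline/follow-up correlation r. Then:

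- slope of change on baseline = −(1 − r)
- correlation of baseline with change = −√((1 − r)/2)
- probability of significance (Fisher z) = Φ(|atanh(correlation)| × √(n − 3) − 1.96)

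Example, r = 0.8 and n = 150: correlation = −√0.1 = −0.316; atanh = 0.3275; 0.3275 × √147 = 3.970; Φ(3.970 − 1.960) = 0.978.

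The same null was simulated as a multiple regression with seven further covariates unrelated to outcome, 1,500 runs per cell. The last three columns give the share of runs in which baseline was significant at 5%.

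| r (assumed) | Slope | Correlation | Fisher z, n = 150 | Simulated, n = 150 | Simulated, n = 100 | Simulated, n = 75 |
|---|---|---|---|---|---|---|
| 0.5 | −0.50 | −0.500 | 100% | 100% | 99.9% | 99.0% |
| 0.7 | −0.30 | −0.387 | 99.9% | 99.7% | 98.2% | 91.3% |
| 0.8 | −0.20 | −0.316 | 97.8% | 96.9% | 86.6% | 77.6% |
| 0.85 | −0.15 | −0.274 | 92.6% | 91.2% | 77.2% | 63.9% |
| 0.9 | −0.10 | −0.224 | 78.7% | 77.3% | 58.1% | 46.9% |
| 0.95 | −0.05 | −0.158 | 48.9% | 48.8% | 34.1% | 26.5% |

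Every cell is well above 5%. The formulas are scale-free, so they apply equally to change in physical activity.

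**What is not affected.** With baseline in the model, taking change or the follow-up score as outcome gives the same coefficients for all other predictors. In a numerical check the other predictor had coefficient 0.150 both ways. Only the baseline coefficient moved, from 0.726 (follow-up score) to −0.274 (change), a shift of exactly −1.

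**Missing data.** The n = 100 and n = 75 columns describe complete cases. The Data analysis section allows single mean imputation as needed. If a missing follow-up score were replaced by the mean, that child's change would be a constant minus baseline, a slope of −1, which strengthens the artefact.

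**A possible separate test.** Under the same null at n = 150, correlating change with the mean of baseline and follow-up (Oldham) rejected in 4–6% of runs.

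**The case against.** The strongest reply has four parts.

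First, a standard multiple regression normally enters all terms together, so baseline already adjusts dosage and programme type whatever list it is on. This stands. A reader might infer that having baseline in the model is itself a fault, or that the other coefficients are biased by it; the identity shown above rules that out. Only the reading of one coefficient is at issue.

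Second, the article nowhere says that low starters benefit most or that programming will be targeted by starting level. Baseline does predict observed change in the plain predictive sense. This also stands: the misreading is invited, not stated. But the Background ties identified predictors to programming decisions, and baseline is put forward as one.

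Third, r is not in the documents. Under a null of equal true gain, r equals the reliability of the score, so values of 0.5–0.8 assume a fairly noisy 22-item scale. A reader might infer that a significant baseline term is a near certainty. That holds only up to about r = 0.8–0.85 with all 150 analysed; at r = 0.9 with 100 analysed it is 58%. Recruitment runs through September 2019 and data collection ends on March 31, 2020, so the latest recruits cannot reach 12 or 24 months.

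Fourth, the sentence on physical activity also covers continued participation. Baseline activity is not that outcome's own baseline, so the coupling does not apply there.

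**Conclusion.** The point holds in a limited form. In the 6–12 cohort, the baseline coefficients for change in physical literacy and change in physical activity will be pulled below zero by regression to the mean, and this design has no control group to separate that from a real effect. With equal true gains and equal variances, the coefficient would be significant in about 97–100% of studies of 150 for r = 0.5–0.8, 77–79% at r = 0.9 and 49% at r = 0.95, and in fewer when fewer complete cases are analysed. It cannot support a statement that low starters gain more.

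A reader might go further and conclude that the main results are compromised. The documents do not support that. The repeated measures ANOVAs of time do not use this term, the dosage and programme-type coefficients are unchanged, and the continued-participation outcome is outside the coupling. This is a fault in a supporting regression. It merits correction because the correction is nearly free and alters what the study may conclude.

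**What to change.** Keep baseline in both change models, but move it to the adjustment list, the role already given to baseline life skills for ages 13–18. State that its coefficient will not be reported or interpreted as an identified predictor of change. For physical literacy, the candidates would then be dosage, programme type and activity level, and the adjustment set would be the four demographic variables already named plus the baseline literacy score. Split the sentence on physical activity so that baseline activity is adjustment only for change in activity; for continued participation its place need not change on this ground. The cost is wording: same data, same models, same estimates for the other predictors.

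If differential gain by starting level is of interest, add a separate analysis labelled exploratory: change against the mean of baseline and follow-up, or the intercept-slope covariance from a mixed model over the available visits. State its assumptions. The Oldham approach relies on equal variances over time and can mislead if true change varies between children, and late recruits will lack later visits. This option is a small amount of extra analysis.

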#### Outcomes

Participants will complete a baseline assessment within 2 weeks of recruitment. Follow-up research assessments will take place at 6 months, 12 months, and 24 months from the baseline assessment with data collection concluding March 31, 2020. Outcomes have been identified based on the program theory illustrated in the MLSE LaunchPad Theory of Change (See Fig. 1). Outcomes and indicators for the primary objectives are detailed in Table 3.

**Table 3 Tab3:** Outcomes for Primary Objectives

Participants aged 6–12	
a) Increased physical literacy	Indicator:
	PLAYself Physical Literacy Assessment for Youth [36] 22-item graded self-report scale used to evaluate level of physical literacy
b) Physical activity minutes/day	Indicator:
	One-week pedometry producing at least 3 days of valid data with a minimum wear time of 10 h/day
c) Continued engagement in sport	Indicator:
	Self-report of regular sport/physical activity participation
Participants aged 12–18	
a) Life skills:	Indicator:
i. Critical Thinking ii. Resilience iii. Self-esteem iv. Self-regulation v. Social Competence vi. Grit	Critical Thinking in Everyday Life Scale [37] 20-item self-report Likert scale used to measure use of critical thinking skills including reasoning, enquiry, analysis/information processing, flexibility, and evaluation Child & Youth Resilience Measure [38] 12-item self-report scale used to measure ability to sustain well-being Rosenberg Self Esteem Scale [39] 10-item self-report Likert scale used to assess global self-esteem Motivation and Self-Regulation Subscale; derived from the School Attitudes Assessment Survey [40] 4-item self-report Likert scale used to measure ability to initiate and continue behaviours required to achieve academic goals Social Competence Scale for Teenagers [41] 9-item self-report scale used to measure positive social skills necessary to get along well with others and function constructively in groups Grit Scale [42] 8-item self-report scale used to measure stamina in dimensions of effort and interest
b) Academic Performance:	Indicator:
i. School Attendance ii. Academic Performance iii Academic Attainment	Self-report of number of missed school days over past two weeks measured as a percentage GPA as per last report card; failed courses marked as “R” on TDSB report cards will be input as 45% Self-report of highest grade/level completed
c) Physical Outcomes	Indicator:

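### Ages 13–18: correlating life skills and health behaviours with highest grade completed, without adjusting for age, mainly shows how they vary with age

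*Protocol article*

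**What the plan says.** In the Data analysis section for ages 13–18, Pearson coefficients serve to "explore the relationship between each of the life skills, positive health behaviors and academic outcomes". No covariate is attached to them.

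Table 3 (Outcomes) gives three academic indicators for this cohort:
- attendance: "Self-report of number of missed school days over past two weeks measured as a percentage";
- performance: "GPA as per last report card";
- attainment: "Self-report of highest grade/level completed".

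Table 2 lists the attainment indicator as well.

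In the same Data analysis paragraph, the repeated measures ANOVAs are run "controlling for demographic variables such as age, gender, household income and race". The graduation regression is run "while controlling for gender, household income, housing status and baseline life skills score", and the regression for continued sport participation uses the same variables. Age is not listed in either. The moderation analyses name no covariate.

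The Sample size section sets this cohort at 100 youth aged 13–18 (Tables 1 and 3 label it 12–18). The only other planned Pearson correlation is at ages 6–12, to "explore the relationship between physical literacy and physical activity levels". None is planned for ages 19–29.

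**The concern.** A pupil's highest completed grade is set mainly by how old the pupil is. In a cohort covering six single-year ages, most of the variation in this indicator is variation in age. If a life skill score or a health behaviour drifts with age, its raw correlation with grade will differ from zero even if, among pupils of the same age, it has nothing to do with schooling.

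The coefficient would then be read as support for a link from life skills to attainment, which is part of the programme's rationale, when it shows only that older youth score differently. Nothing else in the stated plan would expose this. The 13–18 ANOVAs cover health behaviours and life skills but not academic outcomes. The graduation regression covers only those expected to graduate during the study and does not list age.

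**Working it through.** The article reports no figure for these correlations, so there is none to reproduce. The check asks what age alone would produce.

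**Inputs from the article:** n = 100; ages 13–18; Pearson coefficients without covariates; the three indicators in Table 3.

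**Assumed, because the article gives no values:**
- correlation of a skill or behaviour with age: 0 to 0.3;
- correlation of grade with age: about 0.8 to 0.97;
- correlation of GPA or attendance with age: 0 to 0.3;
- a two-sided 0.05 test with complete data.

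**Step 1: formula.** With no link at a given age, and linear relations with age,

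r(skill, outcome) = r(skill, age) × r(outcome, age).

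The rejection rate by Fisher's z is approximately Φ(z − 1.96) + Φ(−z − 1.96), where z = atanh(r) × √(n − 3) and √97 = 9.849.

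**Step 2: highest grade completed, by formula.** Take r(grade, age) = 0.96.
- r(skill, age) = 0.2: r = 0.2 × 0.96 = 0.192; z = 0.1944 × 9.849 = 1.915; rejection about 48%.
- r(skill, age) = 0.3: r = 0.3 × 0.96 = 0.288; z = 0.2964 × 9.849 = 2.919; rejection about 83%.

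**Step 3: highest grade completed, by simulation.** 3,000 runs per cell; age uniform from 13 to just under 19; grade = age − 6 plus noise, rounded down and capped at 12; no within-age link. The noise was varied to give three grade–age correlations. Rejection rates of the unadjusted Pearson test:

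| r(grade, age) | r(skill, age) = 0 | 0.1 | 0.2 | 0.3 |
|---|---|---|---|---|
| 0.97 | 4.8% | 16.4% | 49.4% | 84.2% |
| 0.92 | 5.0% | 15.3% | 46.2% | 81.8% |
| 0.82 | 6.0% | 12.5% | 37.0% | 71.6% |

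The mean unadjusted coefficient is 0.16–0.19 when r(skill, age) = 0.2 and 0.25–0.29 when it is 0.3. In the same runs the partial correlation given age averages about 0 and rejects in 4–6% of samples.

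**Step 4: what is left for a real link.** The share of grade variance not explained by age is 1 − r². This is 1 − 0.90² = 19%, 1 − 0.95² = 9.8% and 1 − 0.97² = 5.9%. Any true within-age association has only that share to act through, so the raw coefficient is dominated by age.

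**Step 5: GPA and attendance.** The largest product in the assumed range is 0.3 × 0.3 = 0.09. Then z = 0.0902 × 9.849 = 0.889 and the rejection rate is about 14%. At a product of 0 it is 5%.

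**The case against.** The strongest reply is that this is an exploratory summary. No hypothesis in Table 1 concerns the association of life skills with academic outcomes, and no significance level is stated for these coefficients. That stands: the consequence is a misleading reported association, not a failed confirmatory test. But the coefficient itself is shifted, whether or not a p-value is attached.

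A second reply is that highest grade may not be among the outcomes correlated. Table 1 names attendance, performance and graduation rates under academic outcomes. This leaves some doubt. However, Tables 2 and 3 both list highest grade as an academic indicator, and the analysis text does not exclude it.

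A third is that schooling may be irregular in this population, which includes newcomers, homeless youth and youth in care, and so weaken the tie between grade and age. The 0.82 row of the table allows for this; the rate at r(skill, age) = 0.2 falls from 49% to 37% but stays far above 5%.

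A reader might also infer more than the article supports:
- **That all the academic correlations measure age and not academic success.** GPA and attendance are not functions of age, and their correlations do bear on academic success.
- **That every other analysis adjusts for demographics and only these do not.** The moderation analyses name no covariate, and the 13–18 regressions do not list age.
- **That the 6–12 correlation has the same flaw to the same degree.** It involves no academic outcome. The age-controlled regressions in that cohort already use physical activity as a predictor of change in physical literacy, and physical literacy as a predictor of change in activity.

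**Conclusion.** The point holds for one indicator in one cohort. At ages 13–18, the unadjusted correlation of a life skill or health behaviour with highest grade completed mainly describes how that skill or behaviour changes with age. The size depends on a skill–age correlation the article does not report: about 37–49% false significance at 0.2, 72–84% at 0.3, and about the nominal 5% if there is no age drift. These figures assume a two-sided 0.05 test, 100 complete pairs and a grade–age correlation between about 0.82 and 0.97.

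GPA and attendance are mildly exposed, at 5–14%, under assumed age correlations of up to 0.3. The 6–12 correlation is a minor consistency point. Because the analysis is exploratory, this is a correction worth making for its low cost and does not threaten a primary test.

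**What to change.** In the Data analysis text for ages 13–18, replace the raw Pearson coefficients with partial correlations given age, using age at the visit where both variables were measured. This is essential for highest grade completed; apply it to GPA and attendance so that all three are reported alike. State in that sentence which academic indicators are included. The same change to the physical literacy and physical activity correlation at ages 6–12 is optional.

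The cost is one degree of freedom per covariate. No new data are needed, since age is already a planned covariate in the ANOVAs, and the analysis can keep its exploratory label. Expressing attainment as grade relative to that expected for age is a possible addition, but it would need an expected-grade rule that the article does not give, so it is not required.
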